### Anesthesia

An arterial catheter will be inserted into patients’ radial artery or dorsal pedis artery under local anesthesia without sedation. Intraoperative monitoring includes 5-lead electrocardiogram, invasive arterial blood pressure, pulse oximetry and train of four (TOF) stimulation. Anesthesia is induced with 1-2 mg/kg propofol, 0.2 mg/kg etomidate, 1–1.5 mg/kg lidocaine and 0.3ug/kg sufentanil and 0.15 mg/kg cisatracurium. After preoxygenation with pure oxygen, patients’ trachea is intubated with a double lumen tube of appropriate side and size. Sevoflurane and remifentanil are used for anesthesia maintainence throughout the entire surgical procedure. Inhaled concentration of sevoflurane are adjusted to maintaining bispectral index(BIS) value within the range of 40 to 60. 0.03 mg/kg cisatracurium is intravenously injected intermittently to keep TOF ratio within T1 to T3.

Lactate ringer’s solution is infused intraoperatively, the infusion rate of which is adjusted to sustaining urine output above 0.5 ml/kg/h. The range of intraoperative mean arterial pressure (MAP) fluctuation is held within 20% from baseline. Intraoperative heart rate is sustained within 50-100 bpm. Norepinephrine is infused continuously to avoid hypotension. A single dose of 4-8ug norepinephrine is injected when necessary. Esmolol is used to treat hypertension after intubation, while a single dose of 0.03 mg/kg nicardipine is injected to treat hypertension during emergence. Infusion of norepinephrine is slowed down or halted upon the occurrence of hypertension. If significant drop in blood pressure is not observed a few minutes later, a single dose of 0.1ug/kg sufentanil is infused or the infusion rate of remifentanil is elevated as an alternative. If hypertension is not attenuated after a few minutes, esmolol (in the case of tachycardia) or nicardipine is used. In the case of conjunction of bradycardia (heart rate < 50 bpm) and hypotension, a single dose of 5-10 mg ephedrine is injected. Anisodamine is injected when bradycardia occurs without the presence of hypotension. In the case of conjunction of tachycardia (heart rate > 100 bpm) and hypotension, the infusion rate of lactate ringer’s solution is elevated or a single dose of 40ug phenylephrine is injected.

Inhalation of sevoflurane is stopped when the surgery is coming to an end, while the infusion rate of remifentanil is maintained at 0.05ug/kg/min from the end of the surgery to extubation. If T4/T1 remains below 90% during emergence, neostigmine in combination with atropine is injected to antagonize residual muscle relaxant effect. However, if myodynamia recovers fully, residual muscle relaxant effect will not be antagonized.

### Mechanical ventilation

During the interval between intubation and the change of body position, all patients are ventilated in pressure-controlled volume-guaranteed mode with 5cmH_2_O PEEP, with I:E fixed to 1:2, and respiratory rate adjusted in order to maintain blood carbon dioxide concentration within the range of 35-45 mmHg. Tidal volume is set to 8 ml/kg during two lung ventilation, both in supine and lateral decubitus positions. During one lung ventilation, tidal volume is set to 4-5 ml/kg.

After intubation in supine position, the tube lumen of the dependent lung is clamped; meanwhile, the operated lung is ventilated with pure oxygen until exhaled concentration of oxygen reaches 100%. Then, the tube lumen of the operated lung is clamped and FiO_2_ is immediately lowered to 0.4. In the meantime, fresh air flow is set to maximum to accelerate the decreasing of oxygen concentration in the ventilated lung. As soon as exhaled oxygen concentration reaches 0.4, both tube lumens are clamped, and patients are disconnected from the ventilator. Subsequently, patients are placed in lateral decubitus position followed by reconnection to the ventilator. The clamps on tube lumens are not removed until patients are reconnected to the ventilator. During the changing of body position, patients’ spine is kept in a straight line to avoid flexion and extension of the neck to prevent the displacement of the double lumen tube, which thereby reduces the time required to readjust the position of the tube. After confirming the position of the double lumen tube in lateral decubitus position, patients are ventilated according to their group assignment. Patients in both groups are ventilated with pure oxygen after adjusting the position of the double lumen tube in lateral decubitus position.

The moment after two lung ventilation is resumed, FiO_2_ is lowered to the largest extent (above or equal to 0.4) while not causing hypoxemia (SpO_2_ < 94%). During emergence, all patients are ventilated in synchronized intermittent mandatory ventilation (SIMV)-volume-guaranteed mode, with PEEP remaining the same with that of the intraoperative level, and FiO_2_ fixed till extubation unless hypoxemia occurs during emergence.

### Intervention

For patients in both groups, one lung ventilation is initiated after readjusting the position of the double lumen tube in lateral decubitus position, The lumen to the independent lung remain closed to air during the interval between intubation to pleural opening. It’s opened to air for 2 min after pleural opening, and subsequently connected with the apneic oxygen insufflation device, which delivers pure oxygen to the independent lung at a constant rate of 5L/min. The dependent lung is ventilated in pressure-controlled volume-guaranteed (PCV-VG) mode, with a tidal volume of 4-5 ml/kg, I:E set to 1:2, and respiratory rate adjusted to maintain end-expiratory carbon dioxide within the range of 30-40 mmHg.

For patients in the study group, individualized PEEP titration is started right after the start of one lung ventilation. The initial PEEP is set to 15cmH_2_O. Subsequently PEEP is lowered at steps of 2cmH_2_O every 3 min. Before changing the level of PEEP, Cstat is calculated according to the formula (Cstat = VT/Pplat-PEEP). When Cstat ceases rising with the continuous lowering of PEEP but starts to drop, the previous PEEP level at which Cstat reaches its zenith is selected as the ideal PEEP (Fig. 2). Then PEEP is elevated to ideal PEEP and kept constant towards the end of the procedure.

**Fig. 2 Fig2:**
[figure not shown]
Individualized PEEP titrated to maximize Cstat. *RM* ventilator driven recruitment maneuver, *PEEP* positive end expiratory pressure, *iPEEP* individualized PEEP, *Cstat* static lung compliance

For patients in the control group, PEEP is set to zero before pleural opening. Right after pleural opening, the dependent lung undergoes RM in pressure-controlled mode, driving pressure set to 20cmH_2_O, PEEP initially set to 5cmH_2_O and raised at steps of 5cmH_2_O and maintained for 10 breathing cycles for each step. When PEEP reaches 20cmH_2_O and plateau reaches 40 cmH_2_O, PEEP level is maintained for 15 breathing cycles towards the end of RM (Figs. 3 and 4), followed by iPEEP titration consistent with that of the study group.

**Fig. 3 Fig3:**
[figure not shown]
The ventilator-driven alveolar recruitment maneuver protocol. *P peak* Peak airway pressure. *Pplat* Plateau airway pressure. *PEEP* Positive end-expiratory pressure. *Vt* Tidal volume normalized for adjusted body weight. *I:E* Ratio between inspiratory and expiratory time. *RR* Respiratory rate

**Fig. 4 Fig4:**
[figure not shown]
Intervention and perioperative management. *Group S* study group, *Group C* control group, *DLT* double lumen tube, *TLV* two lung ventilation, *AOI* apneic oxygen insufflation, *RM* ventilator driven recruitment maneuvers, *PEEP* positive end expiratory pressure, *iPEEP* individualized PEEP

### Protocol deviation

Anesthesiologists can deviate from the trial protocol whenever concerns over patients’ safety emerge. During one lung ventilation, if hypoxemia(SpO_2_ < 92%) persists after excluding displacement of double lumen tube, rescue recruitment maneuvers could be performed. Subsequently, two lung ventilation can be resumed temporarily in case hypoxemia is not corrected. Patients who deviate from the protocol will be excluded from the final analysis.

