### Study population

Patients scheduled for elective video-assisted pulmonary lobe resection under general anesthesia will be screened and recruited during routine preoperative assessment. During recruitment, we will cooperate with surgeons to obtain detailed medical history and results of laboratory tests and radiological tests. Furthermore, we will discuss the procedures of our trial intervention with other anesthesiologists of our center, thereby receiving assistance from collegues during the trial implemention. With the help of collegues, reaching sample size wouldn’t be difficult. The inclusion criteria are as follows: 18–75 years old, American society of anesthesiologists (ASA) grade III or lower, double lumen tube used for lung isolation, length of one lung ventilation exceeding that of two lung ventilation, anticipated to undergo one lung ventilation for over an hour.

Exclusion criteria: pregnant, history of chronic obstructive pulmonary disease (COPD) (defined as GOLD grades III-IV), with pulmonary fibrosis, requiring devices other than double lumen tube for lung isolation, with bulla on the dependent lung, with severe pneumothorax or emphysema, with congestive heart failure (defined as NYHA grades III-IV), having a history of pulmonary surgery, a history of acute respiratory infection (within one month prior to surgery), dependent on renal replacement therapy, pulmonary arterial hypertension (defined as mean pulmonary arterial pressure exceeding 25 mmHg during rest or systolic pulmonary arterial pressure over 40 mmHg), known or suspected neuromuscular illnesses (thymoma, myasthenia gravis, myopathy, myodystrophy), planned for postoperative mechanical ventilation, scheduled for bilateral surgery, scheduled for surgery in prone position, sustained hemodynamic instability or refractory shock (according to the judgement by the anesthesiologist in charge), known significant lung injury (PaCO_2_ > 50 mmHg, PaO_2_ < 50 mmHg), taking angiotensin converting enzyme inhibitor (ACEI) or angiotensin receptor blocker (ARB) to treat hypertension.

Dropout criteria: unplanned thoracotomy conversion, intraoperative blood loss surpassing 500 ml.

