#### Strategies to improve adherence

The two main reasons for investigators to deviate from trial protocol are the occurrence of hemodynamic instability and refractory hypoxemia. So, during the pre-op visit, patients at risk for massive bleeding and hemodynamic instability should be identified. In addition, patients should be screened for risk factors of hypoxemia during one lung ventilation.Protocol amendments.

The primary investigator would notify all members of the research team, the ethics committee, and the surgeons, nurses and other anesthesiologists of our center who provide assistance to the implementation of the trial. After notification, a copy of the revised protocol would be added to the investigator site file.

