### Sample size calculations

The primary endpoint of this study is oxygenation index measured at T4. According to literature [16], oxygenation index for patients inhaling pure oxygen and under well oxygenated conditions during TLV usually ranges between 350-400 mmHg and drops to 150-200 mmHg after patients are switched to OLV. Therefore, during OLV, changes in oxygenation index within the limit of 50 mmHg would be clinically insignificant. Thus, the cut-off value for inferiority is set to 50 mmHg. In other words, in our study, if oxygenation index measured at T4 of the study group is below that of the control group, but the difference between that of the two groups is within 50, then the ventilation strategy of the study group is not inferior to that of the control group in terms of improving intraoperative oxygenation. We set probability of type 1 error at α = 0.025, probability of type 2 error at β = 0.20, and power value at 0.80; a sample size of 38 is calculated for each group by using PASS 11.0 software. Considering a 10% removal and dropout rate, a final sample size of 42 is required for each group.

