### Statistical analysis

The research team will cooperate with medical statisticians to analyze data after completing the trial. SPSS 20.0 software will be applied for data processing. Dropout or lost to follow up cases will be reported. Per-protocol analyses will be applied for all data. Under circumstances of missing values, multiple imputation shall be conducted. Kolmogorov–Smirnov analysis will be performed to discern normally distributed data. Normally distributed data will be presented as mean $$\pm$$ standard deviation (SD), while discrete data will be presented as median and interquartile range. Independent-samples T test will be adopted for univariate analysis of normally distributed data. Pearson correlation test will be used to test the linear relationship between two variables. Mann–Whitney U test will be applied for discrete data. Categorical variables will be expressed as relative risk ratio and assessed by Fisher’s exact test or chi-square tests, if applicable. 95% CI will be employed to express confidence level of all parameters. *P* value < 0.05 shall be defined as statistically significant.

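### Patients rescued for hypoxemia are removed from the only analysis of an oxygenation endpoint, so the non-inferiority test is biased whenever rescue rates differ by arm

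*Protocol article*

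**What the plan says.** Four statements in the protocol article fix the rule.

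- **Protocol deviation.** If saturation stays below 92% during one lung ventilation once tube displacement is ruled out, "rescue recruitment maneuvers could be performed", followed if needed by a temporary return to two lung ventilation. The section ends: "Patients who deviate from the protocol will be excluded from the final analysis". The sentence carries no qualifier.
- **Strategies to improve adherence.** On why deviations are expected, this section says: "The two main reasons for investigators to deviate from trial protocol are the occurrence of hemodynamic instability and refractory hypoxemia".
- **Statistical analysis.** "Per-protocol analyses will be applied for all data". No as-randomised analysis is named. On missing data: "Under circumstances of missing values, multiple imputation shall be conducted"; nothing extends this to excluded patients.
- **Sample size calculations.** "The primary endpoint of this study is oxygenation index measured at T4". The margin is 50 mmHg, alpha 0.025 and power 0.80, giving 38 per group and 42 after a 10% allowance for removal and dropout.

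A further rule under Study population also removes randomised patients: "Dropout criteria: unplanned thoracotomy conversion, intraoperative blood loss surpassing 500 ml".

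**The concern.** The endpoint measures oxygenation, and the rescue that leads to exclusion is triggered by failing oxygenation. Both arms breathe pure oxygen during one lung ventilation (Mechanical ventilation), so a patient whose saturation stays below 92% will tend to sit in the low tail of the oxygenation index. The rule cuts that tail before the means are compared.

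The rescue is also, in kind, the component that the study strategy omits. The trial asks whether the recruitment maneuver can be left out. A study-arm patient who then needs one is direct evidence against that strategy, and the rule deletes that evidence. Incidence and duration of hypoxemia and postoperative pulmonary complications, all secondary endpoints, would be analysed in the same reduced set.

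At stake is the primary conclusion. If the study strategy is truly worse by the margin and its low values are removed more often, the trial declares non-inferiority more often than the planned 2.5%.

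**Working it through.** **1. The plan's own figure.** No SD is stated, so the 38 per group cannot be checked independently. It can be inverted, reading alpha 0.025 as one-sided and the true difference as 0:

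SD = margin × √(n/2) / (z₀.₉₇₅ + z₀.₈₀) = 50 × √19 / (1.960 + 0.842) = 77.8 mmHg.

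An SD of 77 to 77.8 reproduces 38. The t-based formula needs 76 to 76.5, and a two-sided alpha of 0.025 needs about 70. I use 77.8.

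**2. Assumptions that the documents do not give.** T4 index normal with the same SD in both arms; true difference -50 mmHg (the edge of the null); 42 per arm; rescue when a latent oxygenation value falls below one threshold common to both arms; correlation ρ between that value and T4 of 1.0, 0.7 or 0.4; study-arm exclusion of 5-20%. With a common threshold, the control-arm exclusion follows from the 50 mmHg difference.

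**3. Shift in the estimate.** Deleting the lowest fraction p of an arm raises its mean by ρ × SD × φ(a)/(1 − p), where a is the normal quantile of p. For p = 10% in the study arm:

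- Study: a = −1.282, lift = 77.8 × 0.1755/0.90 = 15.2 mmHg.
- Control: the same threshold is (−50 − 1.282 × 77.8)/77.8 = −1.924 SD from the control mean, so 2.7% are excluded and the lift is 5.0 mmHg.
- Expected estimate at ρ = 1.0: −50 + 15.2 − 5.0 = −39.8. At ρ = 0.4: −50 + 0.4 × 10.2 = −45.9.

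**4. Error rate by simulation.** 20,000 trials per scenario, pooled t, non-inferiority declared when the lower 95% limit exceeds −50. Cells show mean estimate and false non-inferiority rate.

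| Excluded, study (control) | ρ = 1.0 | ρ = 0.7 | ρ = 0.4 |
|---|---|---|---|
| none | −49.8; 0.025 | – | – |
| 5% (1%) | −44.0; 0.054 | −45.7; 0.046 | −47.5; 0.034 |
| 10% (3%) | −39.8; 0.091 | −43.1; 0.061 | −46.0; 0.040 |
| 15% (5%) | −36.7; 0.135 | −40.7; 0.077 | −44.7; 0.050 |
| 20% (7%) | −33.9; 0.173 | −38.8; 0.095 | −43.7; 0.054 |

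A repeat with 60,000 trials and another seed agreed to within simulation error (for example 0.180 for 20% at ρ = 1.0, and 0.055 at ρ = 0.4).

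**5. Direction check.** With the exclusion rates set separately by arm, ρ = 1.0 and a true difference of −50:

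- 10% in each arm: estimate −50.0, error 0.027 (no material bias).
- 10% of control and 5% of study: estimate −56.8, error 0.009 (bias against non-inferiority).

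**The case against.** **Direction.** A reader might infer that the trial is biased toward non-inferiority outright, because the study arm gets no planned recruitment maneuver. The documents do not support that. The exclusion rule covers both arms. Control patients start one lung ventilation at the same point on pure oxygen but at zero PEEP until pleural opening (Intervention), so they too can become hypoxemic and be removed before their planned maneuver. The other main reason given for deviating is hemodynamic instability, and the Discussion says recruitment maneuvers can cause it. Step 5 shows that the bias vanishes with equal rates and reverses if control is excluded more. This objection stands, and the claim is conditional.

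**Size.** Much larger error rates can be produced, but one of about 26-28% needs some 28-30% of the study arm excluded and a correlation of 1.0, whereas the plan allows for 10% removal and dropout. Rescue can occur at any time in one lung ventilation while the endpoint is a single T4 sample, so the correlation may well be below 1. This stands too, and is why the range runs down to 3%.

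**Per-protocol is customary in non-inferiority trials.** That is true, and using it is no fault. The fault is that it is the sole analysis and that one of its exclusions depends on the outcome, so it cannot be presumed conservative.

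**Neighbouring rules.** Thoracotomy conversion and blood loss over 500 ml may discard valid T4 values, but nothing shows that they depend on oxygenation or differ by arm, so they do not support the bias. The criterion "length of one lung ventilation exceeding that of two lung ventilation" might be read as a further exclusion after surgery. It sits in a list applied at preoperative screening, and no text removes patients for failing it later, so it forms no part of this point.

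**Conclusion.** Wrong as written. The document itself states the rule, so a separate statistical analysis plan would have to contradict the protocol to cure it. Exclusion depends on the outcome being tested, and the comparison is biased whenever hypoxemia rescue differs between arms. The bias favours non-inferiority if the study arm is truly worse or is rescued more often, and opposes it if control is rescued more often. The first case is the one a non-inferiority test exists to control.

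At a true deficit equal to the margin, with 5-20% of the study arm and 1-7% of control excluded through one common trigger, the apparent difference lies between about −48 and −34 mmHg. The error is about 3-6% at correlation 0.4 and 5-18% at correlation 1.0, against a nominal 2.5%. These figures rest on the back-solved SD and on assumed rescue rates and correlations, none of which the documents give. They illustrate the mechanism and do not forecast the result. Because a choice of analysis set made after the results are seen carries little credibility, this should be settled before analysis.

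**What to change.** Replace the last sentence of Protocol deviation and the per-protocol sentence of Statistical analysis with the following:

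- The primary analysis includes all randomised patients in their allocated arm.
- Every recorded T4 value is kept, including in patients rescued after T4, converted to thoracotomy or with blood loss over 500 ml.
- The handling of rescue before T4 is pre-specified, with a tipping-point sensitivity analysis. Using the last value before rescue or assigning an unfavourable value are two options. The second makes the outcome a composite, while the 50 mmHg margin was argued for measured oxygenation, so the choice should be justified.
- Per-protocol is a supporting analysis, and non-inferiority is claimed only if both analyses agree.
- Rescue and all exclusions are reported by arm, with reasons.

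The clinical rescue rule stays as it is. The change needs no extra patients, procedures or measurements. Its cost is a slightly wider confidence interval or some loss of power, from retaining low values and requiring two analyses to agree.

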Secondary endpoints are as follows:Results of blood gas analysis.Qs/Qt (intrapulmonary shunt) (calculated with results of blood gas analysis obtained at each time point).Respiratory parameters (tidal volume (TV), respiratory rate (RR), plateau pressure (Pplat), static lung compliance (Cstat), driving pressure ($$\Delta$$ P)) recorded at the following time points: before and after RM, each step of iPEEP titration, before and after pleura opening, once every 15 min after pleura opening, before and after resuming two lung ventilation, before and after patients are turned into supine position at the end of surgery, before extubation.Anesthesia-associated parameters: hemodynamic parameters, incidence as well as total duration of hypotension, time required for emergence from anesthesia, dose of anesthetics, incidence, and total duration of hypoxemia.Hygienic indicators: incidence of transference to ICU, length of ICU stay, length of hospital stay, and adverse events.PPCs. We define PPCs as follows:Respiratory infection: Two or more of the following for > 48 h: new cough/sputum production, physical findings compatible with pneumonia, fever > 38 $$^\circ{\rm C}$$, and new infiltrations on chest X-ray (CXR).Respiratory failure: Postoperative PaO_2_ < 8 kPa (60 mmHg) on room air, PaO_2_ / FiO_2_ (inspired fraction of oxygen) ratio < 40 kPa (300 mmHg), or arterial oxyhemoglobin saturation measured with pulse oximetry < 90% and requiring oxygen therapy.Pleural effusion: CXR with blunting of costophrenic angle, loss of sharp silhouette of the ipsilateral hemidiaphragm in upright position, displacement of adjacent anatomical structures, or (in supine position) hazy opacity in one hemithorax with preserved vascular shadows.Atelectasis: Lung opacification with mediastinal shift, hilum or hemidiaphragm shift towards the affected area, with compensatory hyperinflation in adjacent non-atelectatic lung.Bronchospasm: Newly detected expiratory wheeze treated with bronchodilators.Aspiration pneumonitis: Acute lung injury after inhalation of regurgitated gastric contents.Pneumonia: CXR with at least one of the following: infiltration, consolidation, cavitation; plus at least one of the following: fever > 38^。^C with no other cause, white cell count < 4 or > 12*10^9^ /L, > 70 yr of age with altered mental status with no other cause; plus at least two of the following: new purulent/changed sputum, increased secretions/suctioning, new/worse cough/dyspnea/tachypnoea, rales/bronchial breath sounds, worsening gas exchange.ARDS: Ventilated, bilateral infiltrates on CXR, PaO_2_:FIO_2_ < 300, minimal evidence of left atrial fluid overload within 7 days of surgery.Tracheobronchitis: Purulent sputum with normal chest radiograph, no intravenous (i.v.) antibiotics.Pulmonary oedema/Pulmonary congestion/hypostasis, acute oedema of lung, congestive heart failure, fluid overload.Exacerbation of pre-existing lung disease.

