### Study visits and data collection

Patients are visited preoperatively, intraoperatively, and postoperatively on postoperative days 1 to 3 and at discharge (Table 1). We collect and record patients’ data at all the above-mentioned time points.Preoperative indicators: age, gender, height, body weight, BMI, ASA status, hypertension, diabetes, chronic hepatic illnesses, gastric esophagus reflux illness, long term use of steroids, history of obstructive sleep apnea (receiving CPAP therapy or not), smoking (current smoker/ have quitted smoking for more than 8 weeks), forced expiratory volume in the first second /forced vital capacity(FEV1/FVC), FVC, preoperative blood gas analysis( PaO_2_, PaCO_2_), hemoglobin, albumin, alanine aminotransferase (ALT), aspartate aminotransferase (AST), urea, creatine.Intraoperative indicators: Time required to achieve satisfactory lung collapse (lung collapse index reaching 8) from the moment of pleura opening, volume of blood loss, urine output, infusion volume (crystalloid fluid, colloid fluid), blood transfusion volume (heterotransfusion, autotransfusion), respiratory parameters (tidal volume, respiratory rate, plateau pressure, PEEP, driving pressure, Cstat, partial pressure of end-expiratory carbon dioxide, arterial blood oxygen saturation), hemodynamic parameters (blood pressure, heart rate, vasopressor), results of blood gas analysis, oxygenation index, Qs/Qt, duration of surgery, duration of anesthesia, duration of one lung ventilation, duration from placement in lateral decubitus position to pleura opening, side of surgery.Postoperative indicators: incidence of PPCs, length of hospital stay, incidence of ICU transference, length of ICU stay.Adverse events: adverse events will be monitored from the initiation of the trial intervention until discharge.

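### Patients rescued for persistent hypoxaemia are excluded as protocol deviators, so the hypoxaemia endpoint loses its own cases and the comparison between arms is distorted in an unknown direction

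*Protocol article*

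**What the plan says.** Four statements in the protocol article bear on this point.

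- **Study endpoints.** The secondary list, among the anaesthesia-related parameters, includes "incidence, and total duration of hypoxemia".
- **Protocol deviation.** For low saturation on one lung the rule is: "if hypoxemia(SpO_2_ < 92%) persists after excluding displacement of double lumen tube, rescue recruitment maneuvers could be performed". If that fails, two lung ventilation may be resumed for a time. The closing sentence, "Patients who deviate from the protocol will be excluded from the final analysis", makes no exception for rescued patients.
- **Strategies to improve adherence.** Here the protocol names the expected causes of deviation: "The two main reasons for investigators to deviate from trial protocol are the occurrence of hemodynamic instability and refractory hypoxemia".
- **Statistical analysis.** The analysis set is fixed in one sentence: "Per-protocol analyses will be applied for all data". No analysis of all randomised patients is named. Dropouts are to be reported and missing values multiply imputed, but nothing says that imputation brings excluded patients back.

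The arms differ in their exposure to hypoxaemia. Under Intervention, study patients start PEEP titration as soon as one lung ventilation begins and have no planned recruitment. Controls also start one lung ventilation in the lateral position, but "For patients in the control group, PEEP is set to zero before pleural opening", and recruitment and titration follow only then.

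**The concern.** The event that the endpoint counts is also the event that triggers rescue, and rescue removes the patient from the analysis. This is selection on the outcome, not ordinary dropout. The patients lost are those whose hypoxaemia persisted enough to be treated.

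The trial asks whether planned recruitment can be omitted without loss of oxygenation. How often, and for how long, patients in each arm became hypoxaemic is a direct safety reading on that question. If the exclusion removes different numbers of cases from the two arms, the only planned analysis of this endpoint cannot show whether omitting recruitment leads to more hypoxaemia.

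**Working it through.** **Step 1: does the rule remove cases of the endpoint?** The rescue steps stand under the Protocol deviation heading, directly before the exclusion sentence. The next section names refractory hypoxaemia as a main reason for deviating. The Statistical analysis section applies the per-protocol set to everything. Every patient excluded by this route had SpO2 below 92% and is therefore a hypoxaemia case. The loss is partial: rescue is optional, so unrescued episodes stay in, as do episodes corrected by repositioning the tube.

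**Step 2: effect within one arm.** The protocol reports no hypoxaemia or rescue rate, so there is no figure of its own to reproduce here. The only input taken from it is n = 42 per arm (Sample size calculations). Let r be the rescued and excluded patients and u the unrescued hypoxaemic patients; both are assumed.

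- Incidence with all patients kept: (u + r)/n
- Incidence after exclusion: u/(n − r)
- Understatement: (u + r)/n − u/(n − r) = r(n − r − u)/[n(n − r)]

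The last expression is positive whenever r > 0 and u + r < n. With u = 4:

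| r | All kept | After exclusion | Understatement |
|---|---|---|---|
| 1 | 5/42 = 11.9% | 4/41 = 9.8% | 2.1 points |
| 2 | 6/42 = 14.3% | 4/40 = 10.0% | 4.3 points |
| 4 | 8/42 = 19.0% | 4/38 = 10.5% | 8.5 points |

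**Step 3: effect on the comparison.** Study versus control, all counts assumed; differences are study minus control:

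| u, r study | u, r control | All kept | After exclusion | Effect |
|---|---|---|---|---|
| 4, 4 | 4, 1 | 8/42 vs 5/42: 19.0% vs 11.9%, +7.1 points | 4/38 vs 4/41: 10.5% vs 9.8%, +0.8 points | Shrunk |
| 8, 4 | 4, 4 | 12/42 vs 8/42: 28.6% vs 19.0%, +9.5 points | 8/38 vs 4/38: 21.1% vs 10.5%, +10.5 points | Widened |
| 3, 2 | 5, 0 | 5/42 vs 5/42: 11.9% in both, RR 1.00 | 3/40 vs 5/42: 7.5% vs 11.9%, RR 0.63 | Created |
| 4, 4 | 6, 1 | 8/42 vs 7/42: 19.0% vs 16.7%, +2.4 points | 4/38 vs 6/41: 10.5% vs 14.6%, −4.1 points | Reversed |

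Exchanging the arms in the first row gives −7.1 and −0.8 points, so the shrinkage works equally in the other direction.

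**Step 4: the same check in rates.** Let h be the true incidence and s the share of hypoxaemic patients who are rescued. Observed incidence is h(1 − s)/(1 − hs). With h = 20% in both arms (RR 1.00), s = 75% in the study arm gives 0.05/0.85 = 5.9%, and s = 25% in the control arm gives 0.15/0.95 = 15.8%, an apparent RR of 0.37. Exchanging the shares gives RR 2.68. Equal shares of 50% give 11.1% in both arms: with equal true incidence and equal rescue shares the ratio survives, but the level is roughly halved.

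**Step 5: duration.** Excluding a rescued patient removes all of that patient's hypoxaemic time, and these episodes had persisted long enough to be treated. The protocol gives no durations, so this part is not quantified.

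**The case against.** **Rescue may not be a deviation.** The text permits rescue in a written two-step pathway, and the adherence section speaks of refractory hypoxaemia, which could be narrower than an episode corrected by one manoeuvre. This is possible but the weaker reading: the heading, the position of the exclusion sentence and the adherence section all point the other way. A study patient given rescue recruitment has also received what that arm is meant to omit.

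**Other exclusions could raise the incidence.** Haemodynamic instability is the other main reason for deviating, and the Study population section adds "Dropout criteria: unplanned thoracotomy conversion, intraoperative blood loss surpassing 500 ml". With u = 20 and r = 1, 21/42 = 50.0% becomes 20/39 = 51.3% once two non-hypoxaemic patients also leave. That mixes two effects. With those two exclusions held fixed, dropping the rescued case still lowers incidence, from 21/40 = 52.5% to 20/39 = 51.3%.

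**The examples are assumed and small.** This stands. By Fisher's exact test none is significant before or after exclusion (p = 0.55 to 1.00, 0.44 to 0.35, 1.00 to 0.71 and 1.00 to 0.74, in table order). The sample size allows 42 − 38 = 4 removals per arm for all causes, and three of the four examples use all of that on rescue in at least one arm. They show what the rule can do to an estimate, not what it will do.

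**The endpoint is minor and its threshold is not given.** It is one secondary item without its own hypothesis or power. The Mechanical ventilation section uses SpO2 below 94% after two lung ventilation resumes, whereas rescue uses below 92%; under a broader definition, rescued patients would be a smaller share of events. Both points limit the weight. The exclusion rule can also affect the primary oxygenation index at T4, which is a separate matter and does not weaken this one.

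**Reporting may mitigate.** Dropouts are reported and adverse events monitored until discharge. Neither guarantees rescue counts by arm or returns the patients to the comparison.

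**Conclusion.** The concern holds. The exclusion and the per-protocol rule are both fixed in the text, so this is not a detail left to a later analysis plan. Together they remove patients from the hypoxaemia endpoint because they had hypoxaemia and were rescued for it.

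Other exclusions held fixed, incidence is understated in any arm with rescues unless every patient in that arm was hypoxaemic, and total duration loses the rescued episodes. The bias in the comparison has no known direction or size, because it depends on how rescued and unrescued cases fall between arms. The calculated examples are illustrations, not bounds. The conclusion rests on reading rescue as a deviation, which the text favours. The change should be made, but the point concerns a secondary endpoint and confidence is medium.

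**What to change.** For hypoxaemia incidence and duration, change the exclusion rule and analysis set as follows:

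- Analyse by assigned group all randomised patients who start one lung ventilation.
- Keep rescued patients in as hypoxaemia events.
- Count all recorded hypoxaemic time, before and after rescue.
- Report the number of rescues by arm, separately for recruitment and for return to two lung ventilation.
- Keep the per-protocol result as a second analysis.

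The cost is wording. No new measurement is needed, since the intraoperative indicators under Study visits and data collection already include "partial pressure of end-expiratory carbon dioxide, arterial blood oxygen saturation". There are two downsides: the reported incidence will be higher than under the present rule, and duration after a rescue partly reflects the rescue treatment and not the assigned strategy. Reporting rescues by arm lets the reader judge the second.
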